## 16.3 Analysis populations

- Intent-to-Treat (ITT) Population: all subjects who are enrolled in the trial.
- Safety Population: all subjects who receive at least 1 dose of trial medication(s).

All efficacy analyses, except for analyses on OR and DR, will be performed on the ITT population.

Analyses on OR will be performed for subjects who receive at least 1 dose of trial medication(s).

Analyses of DR will be performed for overall responders only.

Safety population will be the primary population for evaluating treatment administration/compliance and safety.

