#### **5.2 Secondary Objectives**

To assess:

- toxicity and safety;
- median time to best response;
- median duration of response;
- median progression free survival;
- overall 2 year survival in women with metastatic breast cancer, when treated with

the combination of vinorelbine and sorafenib at optimal doses.

To assess pharmacokinetic steady state parameters and interaction between vinorelbine and sorafenib when administered together at optimal doses.

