## 6. STUDY DESIGN

This will be a non-randomized, open label, phase I/II, multi-centre study of sorafenib in combination with fixed doses of vinorelbine as first-line treatment for women with metastatic breast cancer.

In the Phase I of the study, 6-12 patients will be recruited in a single center (Jewish General Hospital, Montreal).

In the Phase II part, 21-24 more patients will be recruited and treated in six different centers in Quebec.

The first part of the study will test increasing doses of sorafenib, combined with regular administration of vinorelbine at fixed therapeutic doses (30 mg per square meter on days 1 and 8 of 21-day cycles).

Dose escalations will be made in subsequent cohorts of patients, up to the recommended dose for sorafenib monotherapy. Sorafenib doses will be: 200 mg bid (cohort I) and 400 mg bid (cohort 2).

In the second part of the trial, the cohort of patients treated at the recommended dose will be expanded, up to a total of 27 patients treated with this schedule of the combination regimen (see Section 16.2).

Six patients treated at the recommended dose will be assessed for pharmacokinetic analysis.

Clinical follow-up, including physical examination, laboratory testing and evaluation of adverse event will be performed on day 1 and 8 of each cycle.

Patients will have appropriate radiological imaging to document baseline disease within 4 weeks prior to study entry. Radiological imaging will be repeated regularly after every two cycles, until disease progression or unacceptable toxicity, up to 8 cycles (or after at least 4 cycles after achievement of the best response obtained).

Those patients whose disease has not progressed during the combination treatment, will continue receiving sorafenib alone at the dose of 400 mg bid and will be monitored every 42 days, with clinical and radiological follow-up.

All patients will be followed for a minimum of 2 years for survival and residual toxicity.

Safety will be assessed by examination of adverse events, clinical laboratory data, and vital signs. Adverse events, use of growth factors, and changes in laboratory parameters will be summarized and tabulated. Objective response (CR, PR, SD, and PD) will be summarized and tabulated. Time to response, duration of response, time to progression, and survival will be calculated. Kaplan-Meier estimates and curves will be used to present these time-to-event data.

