**16. STATISTICAL CONSIDERATIONS**

## 16.1 Sample size justification for Phase II

A pooled analysis of data available in the literature was performed, selecting for phase II trials with vinorelbine administered as monotherapy as first-line treatment for metastatic breast cancer. From this analysis, an overall response rate of 43.2% is estimated as representative of vinorelbine single-dose activity in this type of patients (188 objective responses out of 435 evaluable patients).

The combination with sorafenib, increasing vinorelbine efficacy, is reasonably expected to improve the response rate compared to vinorelbine monotherapy. Even though the attainment of an objective response does not directly correlate with a real survival advantage for patients, the higher is the advantage in overall response rate for the combination therapy, the more suggestive this would be of a clinical promising synergism.

It is felt that if the two drugs combination would lead to an increase from ~43% to 63% of response rate (+ 20%), this would compel us to further investigate the activity in a randomized trial.

Sample size for the Phase II was determined using simulation, to obtain a power of 80% in order to detect such an increase in response rate with a significance level ( $\alpha$ ) of 0.10.

Based on this assumption, the minimum sample size would be 27 evaluable patients, as shown below:

QuickTime™ and a  
TIFF (LZW) decompressor  
are needed to see this picture.

A binomial test with a nominal 0.10 one-sided significance level will have the power as shown below for various response rates to test the Null hypothesis response rate of 43%, with a sample size of 27 patients.

| Null hypothesis response rate (p0) | Alternative hypothesis response rate (p1) | Power |
|------------------------------------|-------------------------------------------|-------|
| 43%                                | 53%                                       | 40%   |
| 43%                                | 58%                                       | 61%   |
| 43%                                | 63%                                       | 80%   |
| 43%                                | 68%                                       | 92%   |

Standard software package nQuery Advisor was used to calculate the sample size required for this trial.

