## 16.2 Definition of study outcomes

|                         |                                                                                                                                                             |                                                                                                                 |                                                                                                         |                           |                                                                                                            |                                                                                                          |                                 |                       |
|-------------------------|-------------------------------------------------------------------------------------------------------------------------------------------------------------|-----------------------------------------------------------------------------------------------------------------|---------------------------------------------------------------------------------------------------------|---------------------------|------------------------------------------------------------------------------------------------------------|----------------------------------------------------------------------------------------------------------|---------------------------------|-----------------------|
| Objective response (OR) | Confirmed complete response (CR) or partial response (PR), defined according to RECIST criteria, persisting $\geq 4$ weeks after the initial documentation. | Confirmed objective responses plus confirmed stable disease (SD $\geq 24$ weeks), according to RECIST criteria. | Time from the first dose of study medication to the first documentation of an objective tumor response. | Duration of response (DR) | Time from the first dose of study medication to the first documentation of an objective tumor progression. | TTP will be censored at the date of death for patients who have not had objective disease progression.   | Progression-free survival (PFS) | Overall survival (OS) |

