#### **16.5 Analysis of event-free times**

The efficacy analysis will include Kaplan-Meier curves for TTP, PFS and OS, including quartiles for each variable. The 80% confidence interval of the median event-free time will be estimated using the standard error derived by Greenwood's formula. Covariates will not be included in the calculation of median survival time.

Kaplan-Meier analysis (Kaplan and Meier 1958) will be done using PROC LIFETEST in Statistical Application Software (SAS) (SAS Institute, Inc. 1989), or other equivalent statistical package. Other analyses will be done as necessary.

Kaplan-Meier curves and quartiles will illustrate also time to response and duration of response, if a sufficient number of responders is observed.

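### Time to response is the best response in 5.2 but the first in 16.2, and 16.3 as worded analyses it in all enrolled patients, where its median depends on the response rate

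*Protocol*

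**What the plan says.** Three sections of the protocol name the quantity differently.

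- Section 5.2, secondary objectives: "median time to best response".
- Section 6, study design: "Time to response, duration of response, time to progression, and survival will be calculated", with no mention of best response.
- Section 16.2, definitions: "Time from the first dose of study medication to the first documentation of an objective tumor response". The row label is not legible in the table, but the content can only be time to response.

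The analysis set follows from 16.3. It defines "Intent-to-Treat (ITT) Population: all subjects who are enrolled in the trial" and then states "All efficacy analyses, except for analyses on OR and DR, will be performed on the ITT population". OR is moved to patients who received at least one dose. For DR there is a separate line: "Analyses of DR will be performed for overall responders only". Time to response appears in neither exception.

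The method is in 16.5: "Kaplan-Meier curves and quartiles will illustrate also time to response and duration of response, if a sufficient number of responders is observed". No number is attached to that condition.

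The legible censoring lines in 16.2 concern TTP and survival. None concerns time to response.

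**The concern.** There are two separate problems.

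The first is the event. Appendix E gives best overall response its own meaning: the best status recorded up to progression. Time to best response and time to first response are thus different variables, and the protocol uses one as the objective and the other as the definition.

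The second is the analysis set. A patient who progresses or dies without responding on study treatment is not simply someone whose response has yet to be seen. A Kaplan-Meier summary over all enrolled patients must do something with such patients, and either choice departs from how quickly responders respond. Kept at risk, they make the median depend on the response rate. Censored at progression, they are treated as still able to respond, and the curve rises above the true response rate. In addition, an enrolled patient who is never dosed has no time origin, because the clock starts at first dose. OR uses treated patients, so the response rate and the time to response would also rest on different denominators.

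At stake is whether a listed secondary objective gets an interpretable value.

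**Working it through.** **Inputs from the protocol.** Section 16.1 gives n = 27, one-sided alpha 0.10, a null rate of 43% (188/435 = 43.2%, from vinorelbine monotherapy) and a target of 63%. Section 10.2 gives imaging every 6 weeks.

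**The plan's own figure.** Power = Φ[(p1 − p0 − z₀.₉₀√(p0q0/n)) / √(p1q1/n)] = Φ[(0.20 − 1.2816 × 0.0953)/0.0929] = Φ(0.838) = 79.9%, against the stated 80%. This confirms the rates and n used below and has no other bearing on the point.

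**Step 1: the event.** Take a patient with PR at week 6 and CR at week 18. By 16.2 the value is 6 weeks; by 5.2 it is 18. No calculation is needed.

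**Step 2: all patients, non-responders kept at risk.** The all-patient median is the time at which a fraction 0.5/ORR of the responders have responded.

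- ORR 43%: 0.5/0.43 = 1.16, above 1, so there is no median.
- ORR 53%: 0.5/0.53 = 0.94, the 94th percentile of responder times.
- ORR 63%: 0.5/0.63 = 0.79, the 79th percentile of responder times.

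In a sample of 27 the median is reached only with at least 14 responders (13/27 = 48%).

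| True ORR | P(≥14 of 27), exact binomial | Median not reached |
|---|---|---|
| 43% | 23.0% | 77% |
| 53% | 62.4% | 38% |
| 63% | 91.7% | 8% |

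This takes 27 as the size of the set. The upper quartile, also planned in 16.5, needs 75% responding, so in population terms it is not reached even at 63%.

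**Step 3: where the median exists.** Assume ORR 63% and responses at weeks 6/12/18/24. The timings are assumptions; the protocol gives none.

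- Split 55/30/10/5%: cumulative response is 0.63 × 0.55 = 35% at week 6 and 0.63 × 0.85 = 54% at week 12. The all-patient median is 12 weeks; the responder median is 6.
- Split 25% each: cumulative response is 0.63 × 0.75 = 47% at week 18 and 63% at week 24. The all-patient median is 24 weeks; the responder median is 15.

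**Step 4: if non-responders were censored at progression.** This rule is hypothetical. Take ORR 43%, the 55/30/10/5% timing, and 35% of the remaining non-responders progressing at each scan.

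- Week 6: S = 1 − 0.2365 = 0.764
- Week 12: S = 0.764 × (1 − 0.129/0.564) = 0.589
- Week 18: S = 0.589 × (1 − 0.043/0.305) = 0.506
- Week 24: S = 0.506 × (1 − 0.0215/0.178) = 0.445

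One minus Kaplan-Meier ends at 56% against a true 43%, and a median would be read at week 24. With 20% or 10% progressing per scan it ends at 49% or 46%, and there is no median.

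A large-sample simulation varied the assumptions further. Responses were split 50/30/15/5% or 25% each, with exponential progression in non-responders seen at 6-weekly scans. The final value of one minus Kaplan-Meier was:

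| Median time to progression, non-responders | ORR 43% | ORR 63% |
|---|---|---|
| 8 weeks | 61–71% | 80–86% |
| 13 weeks | 53–60% | 73–78% |
| 26 weeks | 47–51% | 68–71% |
| 52 weeks | 45–47% | 65–67% |

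The curve exceeds the true rate in every case. At 43% a median appears at 18–24 weeks in the first row and 24 weeks in the second. In the third row it appears only with even timing, and in the fourth not at all. At 63% censoring moved the median by at most one 6-week visit.

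**The case against.** The strongest reply is that 16.5 already implies responders only. It treats TTP, PFS and OS as the main Kaplan-Meier analyses, pairs time to response with DR in a separate sentence, and makes both depend on the number of responders. Only responders have the end date that 16.2 requires. That is a fair reading of the intent. It does not remove the conflict with 16.3, whose general rule excepts OR and DR by name and restricts DR alone. Nor does the condition change the analysis set: at 43% about 12 responders are expected (27 × 0.43 = 11.6), which might count as sufficient while the all-patient median is not reached.

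A second reply is that a median not reached over all patients is a valid result, and that a responders-only summary conditions on a post-baseline outcome. Both statements are right. The first gives an honest answer to a different question; the second is why the responder summary must be labelled.

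Two stronger readings are tempting and not supported. A reader might infer that the median is expected not to exist. But 43% is the historical rate used as the null; at the 63% the trial is designed to detect, a median exists and is missed in about 8% of samples. A reader might also infer that the plan censors non-responders at progression and so yields a false median. No section says so. The table in 16.2 is partly illegible, and such a rule may sit in an analysis plan not shown, so its absence is not counted as an error. The false median in step 4 also vanishes when progression is slower.

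**Conclusion.** The point holds in limited form.

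The clash between best response in 5.2 and first response in 16.2 is a plain contradiction and rests on no assumption.

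As worded, 16.3 puts time to response in the all-enrolled set. With non-responders kept at risk, its median is undefined for any true response rate below 50%. Above 50% it is a percentile of responder times fixed by the response rate. The non-attainment probabilities (77%, 38% and 8% at 43%, 53% and 63%) rest only on the binomial, on 27 patients and on full follow-up for response. The gaps in weeks between all-patient and responder medians, and any overshoot under censoring at progression, rest on assumed timings and show direction rather than size.

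The endpoint is secondary and descriptive. No decision rule uses it, and neither the primary analysis nor n=27 is touched. It should be corrected, but it does not threaten the trial.

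**What to change.** 1. **Section 16.3:** extend the responders-only sentence, for example: *Analyses of time to response and DR will be performed for confirmed responders only.* Report the median and range descriptively and label them as conditional on response.
2. **If a curve over all patients is wanted:** use cumulative incidence of response, with progression or death without response as competing events, in treated patients so that every patient has a time origin and the denominator matches ORR.
3. **Sections 5.2 and 16.2:** name the same event, for example the first documented response that is later confirmed. If the date of best response is what is wanted, change 16.2 instead and say how PR followed by CR is dated.

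The cost is a few wording changes, with no new data or patients. The drawback is that the responders-only summary is purely descriptive and cannot be read as an effect in all patients.

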#### **16.4 Analysis of primary endpoints**

Confirmed objective responses and stable diseases will be calculated, to determine objective response rate (ORR) and clinical benefit rate (CBR). The 95% confidence interval for ORR and CBR will be constructed using the exact methods.

ORR is defined as the proportion of subjects with confirmed CR or confirmed PR according to the RECIST criteria, relative to the total subjects who receive at least 1 dose of study medication(s).

CBR is defined as the proportion of subjects with clinical benefit response, relative to the total subjects who receive at least 1 dose of study medication(s).

Patients who do not have on-study radiographic tumor re-evaluation (or clinical re-evaluation, when physical examination is indicated to monitor disease state) will be counted as non-responders/non-benefiters in the assessment of ORR and CBR, unless replaced through enrollment of extra-evaluable patients.

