#### **Reporting of results**

All patients included in the study must be assessed for response to treatment, even if there are major protocol treatment deviations or if they are ineligible. Each patient will be assigned one of the following categories: 1) complete response, 2) partial response, 3) stable disease, 4) progressive disease, 5) early death from malignant disease, 6) early

death from toxicity, 7) early death because of other cause, or 9) unknown (not assessable, insufficient data).

All of the patients who met the eligibility criteria should be included in the main analysis of the response rate. Patients in response categories 4-9 should be considered as failing to respond to treatment (disease progression). Thus, an incorrect treatment schedule or drug administration does not result in exclusion from the analysis of the response rate. Precise definitions for categories 4-9 will be protocol specific.

All conclusions should be based on all eligible patients.

Sub-analyses may then be performed on the basis of a subset of patients, excluding those for whom major protocol deviations have been identified (e.g., early death due to other reasons, early discontinuation of treatment, major protocol violations, etc.). However, these sub-analyses may not serve as the basis for drawing conclusions concerning treatment efficacy, and the reasons for excluding patients from the analysis should be clearly reported.

The 95% confidence intervals should be provided.

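### Section 16.4 gives only exact 95% intervals and leaves out the one-sided 0.10 test of 43% that sized Phase II; if that interval were used to judge 43%, exact power at 63% would be about 43%, against 73% for the exact 0.10 test

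*Protocol*

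**What the plan says.** Section 16.1 sets the design. The sample size is chosen "to obtain a power of 80% in order to detect such an increase in response rate with a significance level" of 0.10, for a rise in response rate from about 43% to 63%. It concludes that "the minimum sample size would be 27 evaluable patients". The test is described in the same section: "A binomial test with a nominal 0.10 one-sided significance level will have the power as shown below for various response rates". Its null value is 43%, and it assumes 27 patients. The printed power is 40%, 61%, 80% and 92% at true rates of 53%, 58%, 63% and 68%.

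Section 16.4 defines the objective response rate (ORR) and clinical benefit rate (CBR) and gives one inferential output: "The 95% confidence interval for ORR and CBR will be constructed using the exact methods". It states no null value, significance level, test or responder cut-off, and does not refer back to 16.1.

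Two other places bear on the confidence level. Section 16.5 says of the time-to-event medians: "The 80% confidence interval of the median event-free time will be estimated using the standard error derived by Greenwood's formula". Appendix E, under its heading on reporting of results, says: "The 95% confidence intervals should be provided".

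**The concern.** A one-sided test at 0.10 corresponds to the lower limit of a two-sided 80% interval. A two-sided 95% interval corresponds to a one-sided test at 0.025. The only inference named for the primary endpoint is therefore at a level that does not match the test behind the 27 patients. The 80% level, which does match, is used in 16.5 for the secondary medians.

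Section 16.1 says that the targeted rise in response rate would prompt a randomised trial. With no rule in 16.4, a reader at the end of the study could judge 43% by the test in 16.1 or by the interval in 16.4. For some results the two give different answers, and the choice could be made after the data are known.

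**Working it through.** **Inputs, all from section 16.1 unless stated.** n = 27; p0 = 0.43 (pooled figure 188/435 = 43.2%); p1 = 0.63; one-sided alpha 0.10; printed power 80%. The exact two-sided 95% interval comes from 16.4.

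**1. The printed power.** One-sample normal approximation without continuity correction:

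power = Φ[(p1 − p0 − z·√(p0(1−p0)/n)) / √(p1(1−p1)/n)]

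Here √(0.43×0.57/27) = 0.0953 and √(0.63×0.37/27) = 0.0929. With z = 1.2816, (0.20 − 0.1221)/0.0929 = 0.838, so power is 79.9%. At the other three rates the formula gives 40.9%, 61.6% and 92.3%. All four are within 2 points of the printed values, so the table is reproduced by this approximation.

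**2. The exact 0.10 test.** The cut-off is the smallest k with P(X ≥ k | 27, 0.43) ≤ 0.10. The exact 95% interval (Clopper-Pearson) has its lower limit above 43% only when the same tail is below 0.025.

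| Responders of 27 | P(X ≥ k) at 43% | P(X ≥ k) at 63% | Exact 95% interval | Lower limit of exact 80% interval |
|---|---|---|---|---|
| 15 | 0.131 | 0.842 | 35.3–74.5% | 41.5% |
| 16 | 0.066 | 0.730 | 38.8–77.6% | 45.1% |
| 17 | 0.029 | 0.587 | 42.4–80.6% | 48.8% |
| 18 | 0.011 | 0.430 | 46.0–83.5% | 52.5% |

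The exact 0.10 test rejects from 16 responders, with attained alpha 0.066 and power 73% at 63%. The lower limit of the exact 80% interval passes 43% at the same count, so that interval agrees with the test.

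**3. The 95% interval, if used as the rule.** It excludes 43% only from 18 responders. Attained one-sided alpha is then 0.011, and power is 43% at 63% and 24% at 58%.

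**4. Like for like.** Exact against exact, power at 63% is 73% and 43%. By the normal approximation with z = 1.96, (0.20 − 0.1867)/0.0929 = 0.143, so power is 56%, against 80% in step 1.

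**5. Where the two rules part.** They differ at 16 and 17 responders. At a true rate of 63% the probability of one of these counts is 0.730 − 0.430 = 0.30. The design target itself falls here: 17/27 = 63.0%, with p = 0.029 by the test and a 95% interval from 42.4%.

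**6. Sensitivity.** With p0 = 43.2% the cut-offs remain 16 and 18 (tails 0.069 and 0.012). The cut-off for the 0.10 test moves with the denominator: 15 of 26, 16 of 27, 16 of 28, 17 of 29.

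**The case against.** The strongest reply is that 16.4 only has the intervals constructed. It does not compare them with 43% or attach any decision to them. The test stands in 16.1, part of the same statistical section, and reporting a 95% interval beside a one-sided 0.10 test is ordinary practice. Appendix E is a source for the 95% level. The 80% level in 16.5 is not tied to the design alpha and does not show that 95% is wrong. An SAP, not seen here, may name the test and its cut-off.

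Most of this stands. A reader might infer that the protocol contradicts itself, or that its primary analysis has 43% power. The documents do not support that, because no passage makes the 95% interval the decision rule. A reader might also set 43% against the printed 80% and blame the confidence level for the whole gap. That mixes methods: the 80% is a normal-approximation figure, and the exact test at the stated level has 73%. Nor does any passage make exclusion of 43% by an interval the condition for going on to a randomised trial.

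What does not fall away is the mismatch in stated text. Section 16.4 is the protocol's own account of the primary analysis. It fixes one confidence level, which differs from the level that sized the study, and it neither calls the interval descriptive nor refers to the test. The test appears only as sample-size justification.

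**Conclusion.** The point holds as a mismatch between design and stated analysis. Section 16.1 sizes the trial for a one-sided 0.10 test of 43%, and 16.4 does not carry that test into the primary analysis.

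The consequence is conditional. If the 95% interval is read against 43%, exact power at 63% is 43% instead of 73% (56% instead of 80% by normal approximation), and 16 or 17 responders would reject under 16.1 without the interval excluding 43%. The printed 80% is delivered neither by the exact 0.10 test nor by the exact 95% interval at n = 27.

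These figures assume 27 patients in the denominator. Section 16.4 uses everyone who receives at least one dose and allows extra evaluable patients to replace those not re-evaluated, so the actual number may differ. The point does not settle whether ORR or clinical benefit is the Phase II primary endpoint. Section 5.1 names clinical benefit and 16.1 sizes on response rate; that needs reconciling separately.

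**What to change.** In 16.4:

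- State that the ORR hypothesis is judged by the exact one-sided 0.10 binomial test against 43% from 16.1, with the cut-off for the actual denominator (at least 16 if n = 27; alpha 0.066, power 73% at 63%).
- Report the matching exact two-sided 80% interval beside it. At 16/27 this is 45.1–72.3%.
- Keep the 95% intervals for ORR and CBR, as Appendix E asks, and label them descriptive.

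In 16.1, restate the power at 63% to match the rule used: about 73% for the exact 0.10 test, or about 43% if the sponsor means the 95% interval to decide.

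The cost is a few sentences and one extra interval, with no extra patients. The protocol must then say openly that the decision rests on a one-sided 0.10 level and that exact power is below 80%. If 80% exact power is to be kept, the 0.10 test first reaches it at n = 28 (at least 16 of 28; alpha 0.094, power 80.0%). With the 95% interval as the rule it is first reached at n = 50 (at least 29 of 50; power 81.1%).

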#### **5.1 Primary Objectives**

**Phase I:** To assess the optimal dose of sorafenib in combination with vinorelbine.  
**Phase II:** To assess the clinical benefit (response rate + disease control rate) in women with metastatic breast cancer, when treated with this combination at the optimal doses.

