## 9. THERAPY ADMINISTRATION

### 9.1 Phase I

In the first part of the study patients will test increasing doses of sorafenib, combined with a fixed schedule of vinorelbine.

Vinorelbine will be administered at the dose of 30 mg per square meter on days 1 and 8 of 21-day cycles.

Dose escalations will be made only for sorafenib, in subsequent cohorts of patients, up to the recommended dose for sorafenib monotherapy.

Planned dose levels for sorafenib are: 200 mg bid (cohort 1) and 400 mg bid (cohort 2).

Three patients will be enrolled at the first dose level. In the absence of a dose-limiting toxicity at the end of the first cycle, three patients will be enrolled in the second dose level. If any patient experiences a dose-limiting toxicity, up to three additional patients will be enrolled at the same dose level.

Only in case of dose-limiting toxicity observed in two or more patients in the first cohort, further recruitment will be at the dose of 200 mg qd for sorafenib (cohort –1).

The maximum tolerated dose will be defined when two or more patients in a cohort of six patients experience a dose-limiting toxicity. The recommended dose (RD) for the second part of the study will be the dose level immediately preceding, or, in the absence of a documented maximum tolerated dose, the dose of 400 mg bid.

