### 9.2 Phase II

In the second part of the trial, the cohort of patients treated at the RD will be expanded, up to a total of 27 patients treated with vinorelbine 30 mg per square meter (days 1, 8 q21) plus sorafenib at the RD.

Six patients in this expanded cohort will undergo sample collection for pharmacokinetic analysis of vinorelbine and sorafenib.

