|                         |                                                                                                                                                             |                                                                                                                 | Time from the first time of progression or death as a result of any cause.                              |                           | Time from the first dose of study medication to the first documentation of an objective tumor progression. | Time from study enrollment to time of death as a result of any cause.                                    |                                 |                       |
|                         |                                                                                                                                                             |                                                                                                                 |                                                                                                         |                           |                                                                                                            | Survival time will be censored at the date of the last follow-up visit for patients who are still alive. |                                 |                       |

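### The efficacy sets in 16.3 and 16.4 are not limited to the recommended dose that the Phase II objectives and the 27-patient calculation concern, and CBR is given two denominators

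*Protocol*

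**What the plan says.** The question is tied to one dose. The Phase II primary objective (Protocol 5.1) is clinical benefit in women "when treated with this combination at the optimal doses". The secondary objectives (5.2), which include progression-free survival and 2-year survival, concern "the combination of vinorelbine and sorafenib at optimal doses". Section 9.2 expands the RD cohort "up to a total of 27 patients treated with vinorelbine 30 mg per square meter" plus sorafenib at the RD. Section 16.1 bases its power table for the one-sided binomial test on the same number, 27.

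Phase I belongs to the same trial and uses more than one dose: "Planned dose levels for sorafenib are: 200 mg bid (cohort 1) and 400 mg bid (cohort 2"). There is a contingency level below these. Each level takes three patients, or up to six if a dose-limiting toxicity occurs (9.1).

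The analysis sets carry no dose or phase restriction. Section 16.3 has "Intent-to-Treat (ITT) Population: all subjects who are enrolled in the trial" and then "All efficacy analyses, except for analyses on OR and DR, will be performed on the ITT population". It places OR on subjects with at least one dose. Section 16.4 defines ORR and CBR, each "relative to the total subjects who receive at least 1 dose of study medication(s").

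**The concern.** At least one Phase I cohort will have been treated at a level other than the RD. Those patients are enrolled and dosed, so by the wording of 16.3 and 16.4 they count in ORR, CBR, TTP, PFS and OS. The reported proportions would then describe a mixture of doses, and their denominator would not be the 27 on which the power rests.

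CBR has a second problem. Section 16.3 excepts only OR and DR from the ITT rule, so CBR falls on all enrolled patients. Section 16.4 divides it by dosed patients. Both cannot hold for an endpoint named in the primary objective.

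At stake is whether the main Phase II result answers the stated question, and whether the choice of denominator is settled before the data are seen.

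**Working it through.** **1. The plan's own figure.** Inputs from 16.1: p0 = 0.43, p1 = 0.63, one-sided alpha 0.10, power 80%.

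Normal approximation: n = [(z0.90·√(p0q0) + z0.80·√(p1q1)) / (p1 − p0)]² = [(1.2816 × 0.4951 + 0.8416 × 0.4828) / 0.20]² = 27.08.

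Power at n = 27 by the same method is 40.9%, 61.6%, 79.9% and 92.3% for true rates of 53%, 58%, 63% and 68%. The plan prints 40%, 61%, 80% and 92%, so its figures reproduce.

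**2. Exact baseline for 27 RD patients.** The smallest cut-off with exact one-sided alpha at most 0.10 is 16 of 27 (attained alpha 0.066). Exact power at 63% is 73.0%. This, not the approximate 80%, is the baseline for the exact figures below.

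**3. Size of the literal denominator.** Section 6 gives 6-12 Phase I patients and 21-24 more in Phase II. With 3 or 6 Phase I patients already at the RD, 3 + 24 = 27 or 6 + 21 = 27. One other level adds 3 to 6 patients:
- 27 + 3 = 30, of whom 3/30 = 10% are off-RD
- 27 + 6 = 33, of whom 6/33 = 18% are off-RD

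**4. Effect on the estimate and on power.** The documents give no response rate for the other level, so I assume a range from 43% (no gain over the null rate) to 63% (same as the RD).

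Expected ORR = (27 × 0.63 + m × p_off) / (27 + m). For example, (17.01 + 1.29)/30 = 61.0% and (17.01 + 2.58)/33 = 59.4%.

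Power is the upper tail of the sum of Binomial(27, 0.63) and Binomial(m, p_off), with exact cut-offs re-derived at p0 = 0.43: 17/30 (alpha 0.093) and 19/33 (alpha 0.066).

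| Assumed off-RD rate | ORR, n=30 | Power, 17/30 | ORR, n=33 | Power, 19/33 |
|---|---|---|---|---|
| 43% | 61.0% | 75.4% | 59.4% | 65.5% |
| 53% | 62.0% | 78.7% | 61.2% | 73.0% |
| 63% | 63.0% | 81.9% | 63.0% | 79.7% |

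The ORR shift is 0 to 2.0 points at n=30 and 0 to 3.6 points at n=33. The standard error at n=27 is √(0.63 × 0.37/27) = 9.3 points.

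At n=33 the attained alpha matches that of the 27-patient rule, so the two compare directly: power is below 73.0% only when the off-RD rate is below about 53%. At n=30 power is not lower, though attained alpha is higher (0.093 against 0.066).

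**5. CBR.** No arithmetic is needed. Section 16.3 gives all enrolled; 16.4 gives all dosed. The two differ by the patients enrolled but never dosed.

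**The case against.** The best defence is that the plan, read as a whole, already identifies the Phase II cohort. Sections 5.1, 5.2, 9.2 and 16.1 all point to 27 patients at the RD, and 16.3 and 16.4 may only be saying which of those 27 count. Nothing says that other dose levels are to be pooled, and analysis sets by phase are often left to the SAP. This makes an RD-only intention likely. It does not remove the conflict, because the protocol itself fixes the sets as everyone enrolled in the trial, or everyone dosed, and an SAP that followed it would inherit that wording.

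On CBR, 16.4 is the more specific text. Registration follows completed pretreatment procedures and eligibility review (6.1), so few patients should be enrolled and never dosed. That limits the size of the conflict without resolving it.

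Three stronger readings are tempting but not supported:
- **That pooling costs power in general.** This comes from setting exact power for the mixed set against the plan's approximate 80%. Against the exact 73.0%, there is no loss at n=30.
- **That the false-positive rate is inflated.** This requires a cut-off derived for 27 patients to be applied to 30 or 33. The protocol states no cut-off, and its exact 95% confidence intervals adapt to whatever denominator is used.
- **That OS has the wrong origin.** OS is defined as "Time from study enrollment to time of death as a result of any cause", which is an accepted convention. The PFS row of the outcome table cannot be read reliably in the text available, so nothing is built on it.

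**Conclusion.** The point stands as a should-fix. The stated efficacy sets do not match the plan's own dose-specific objectives and 27-patient calculation, and CBR has two denominators. Both follow from the text without assumption.

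The numerical effect is modest. At least 82% of the literal denominator is still at the RD, and any bias in ORR is small beside its sampling error. Its size depends on an off-RD response rate that the documents do not give; if response is the same at both levels, the estimate does not shift. The power comparison applies to ORR only, since 16.1 states no test for CBR, PFS or OS.

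One minor consequence of the ITT rule remains: TTP starts at first dose (16.2), so it is undefined for anyone enrolled and never dosed.

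**What to change.** In 16.3 and 16.4:
- Define a Phase II efficacy set: all patients assigned to the RD, including Phase I patients who started at that dose, who received at least one dose.
- Use it as the denominator for ORR and CBR.
- Restrict TTP, PFS and OS to RD patients as well.
- Tabulate efficacy at other dose levels separately.
- Keep all treated patients in the safety set.
- Add CBR to the exceptions in the ITT sentence of 16.3, so that the 16.4 denominator is the only one.

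The cost is a few sentences. No patients, visits or data are added, and the 27-patient calculation is unchanged. Patients at other levels are described separately instead of pooled.
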